## Abstract

**Background:**

Gait and mobility impairments affect the quality of life (QoL) of patients with progressive multiple sclerosis (MS). Robot-assisted gait training (RAGT) is an effective rehabilitative treatment but evidence of its superiority compared to other options is lacking. Furthermore, the response to rehabilitation is multidimensional, person-specific and possibly involves functional reorganization processes. The aims of this study are: (1) to test the effectiveness on gait speed, mobility, balance, fatigue and QoL of RAGT compared to conventional therapy (CT) in progressive MS and (2) to explore changes of clinical and circulating biomarkers of neural plasticity.

**Methods:**

This will be a parallel-group, randomized controlled trial design with the assessor blinded to the group allocation of participants. Ninety-eight (49 per arm) progressive MS patients (EDSS scale 6–7) will be randomly assigned to receive twelve 2-h training sessions over a 4-week period (three sessions/week) of either: (1) RAGT intervention on a robotic-driven gait orthosis (Lokomat, Hocoma, Switzerland). The training parameters (torque of the knee and hip drives, treadmill speed, body weight support) are set during the first session and progressively adjusted during training progression or (2) individual conventional physiotherapy focusing on over-ground walking training performed with the habitual walking device. The same assessors will perform outcome measurements at four time points: baseline (before the first intervention session); intermediate (after six training sessions); end of treatment (after the completion of 12 sessions); and follow-up (after 3 months from the end of the training program). The primary outcome is gait speed, assessed by the Timed 25-Foot Walk Test. We will also assess walking endurance, balance, depression, fatigue and QoL as well as instrumental laboratory markers (muscle metabolism, cerebral venous hemodynamics, cortical activation) and circulating laboratory markers (rare circulating cell populations pro and anti-inflammatory cytokines/chemokines, growth factors, neurotrophic factors, coagulation factors, other plasma proteins suggested by transcriptomic analysis and metabolic parameters).

**Discussion:**

The RAGT training is expected to improve mobility compared to the active control intervention in progressive MS. Unique to this study is the analysis of various potential markers of plasticity in relation with clinical outcomes.

**Trial registration:**

ClinicalTrials.gov, identifier: NCT02421731. Registered on 19 January 2015 (retrospectively registered).

**Electronic supplementary material:**

The online version of this article (doi:10.1186/s13063-017-1838-2) contains supplementary material, which is available to authorized users.

## Background

Multiple sclerosis (MS) is a chronic inflammatory disease causing widespread degeneration of the central nervous system. The disease, with different features and progression according to the clinical phenotype [1], gradually results in severe neurological deficits [2] with complex, variable and unpredictable patterns of symptoms [2] including different motor deficits [1]. Locomotor disability and balance disorders affect approximately 75% of persons with MS, with altered coordination of posture and gait [3, 4], mobility problems [5, 6], reduced walking competency [3] and increased risk of falling [7]. In progressive MS, the high prevalence of motor disorders and gait disabilities, the negative impact on personal activities and quality of life (QoL), and the limited effects of specific medications [8] make gait rehabilitation a crucial part of the management. The aim is to increase patients’ levels of activity and independence [9] and their QoL, even independent of symptom regression [10, 11]. Gait disabilities showed improvement following physical therapy [4, 12–14] and low-to-moderate-intensity aerobic over-ground or treadmill training, which represents a useful option for rehabilitation, also in combination with body weight support [15–17]. To this end, a robot-driven gait orthosis was recently developed, studied and considered a feasible and effective therapeutic option in MS subjects with severe walking disabilities. Robot-assisted gait training (RAGT) allows a more effective support of walking movements and imitation of a nearly normal gait pattern during treadmill training at a higher speed, with improvements in walking distance, velocity and knee extensor strength compared to conventional therapy [18, 19]. Several studies have tested in samples of MS patients the effects of interventions, such as treadmill training [4], bodyweight-supported training on a treadmill [20, 21], RAGT [18, 19, 22–26], or both treatments combined within a single session [27], reporting small but positive effects on functional status [4, 18–20, 23–26] or QoL [10, 21]. Recently, improvements were reported in the 6-min Walking Test and in the balance domain after RAGT [25] but not in gait speed measured by the 10-m Walk Test [26]. Unfortunately these studies, using different devices and training protocols (12 to 15 sessions over 3–6 weeks), including heterogeneous MS subgroups with a limited number of subjects and a wide range of gait disabilities (Expanded Disability Status Scale, EDSS 3–7.5), failed to offer an exhaustive evidence of the superiority of RAGT over other specific gait trainings, so larger trials are necessary [28]. Otherwise, this might be partially explained by the fact that the rehabilitation process in MS subjects is complex and person-specific [28] as the response to treatments regarding neuronal plasticity is highly individual. Functional recovery in MS is achieved by repair of damage through remyelination, with resolution of inflammation and functional reorganization. Evidence from brain systems supports an adaptive role for neuroplastic changes in MS despite its widespread pathology. Specifically, it may limit the negative effects of MS on behavior [29–32] and differs between patients and various disease types, with lower response according to patient age and disease duration [33, 34]. Moreover, different rehabilitation treatments might switch on different adaptive response. High-intensity interventions might be more effective on neural reorganization and motor recovery involving synaptic transmission and formation of novel synapses, cortical reorganization and induction of neurogenesis limited to the site of injury or involving distant healthy brain regions [35]. The effects of neuroplasticity-based technologies and interventions, virtually beneficial for functional recovery, have been poorly tested so far. Different tools, such as positron emission tomography and functional magnetic resonance imaging, could be appropriate to evaluate such recovery-related processes. Several studies have employed these techniques, revealing that in MS patients a decreased hemispheric lateralization [32] and an increasingly bilateral activation, even for simple motor tasks involving higher-control sensorimotor areas, were observed [36, 37]. Other noninvasive, reliable and less expensive measurements, such as transcranial magnetic stimulation and near-infrared spectroscopy (NIRS), could also be useful. In a NIRS-based study the coherence, considered a potentially useful marker in disorders with white matter damage or axonal loss, was found to be similar in MS subjects and controls in the resting phase, but significantly decreased during motor tasks [38]. Moreover, relevant information to identify patterns of recovery in MS patients could be added by the measurement of molecular regulators of neuronal or vascular plasticity. These biomarkers derived from blood tests include circulating cell subsets and soluble factors measurable in plasma. Previous studies involving MS subjects showed that the *N*-acetylaspartate concentration correlated with an increased lateralization index; neurotrophins that regulate neural plasticity, such as brain-derived neurotrophic factor (BDNF) [39], were found in lower concentrations compared to healthy subjects [40]. Furthermore, inflammatory cytokines, such as interleukin-1β, negatively interact with BDNF and amyloid-β has been observed in multifocal MS lesions [41, 42]. Finally, growth factors participate in neural cell survival and tissue repair processes [43–45] and, in particular, platelet-derived growth factor decreases with disease duration, being low in primary progressive MS patients [46] while incomplete glucose oxidation by glycolysis and mitochondria results in increased oxidative stress that promotes lesion progression rather to repair [47–49]. Also, disturbances of the hemostatic mechanisms, which are closely and reciprocally related to inflammation, are relevant for neurological disorders, in particular procoagulant factors and receptors, as well as main anticoagulant proteins endowed with anti-inflammatory activities, that exert cytoprotective effects and favor endothelial barrier stabilization, neurogenesis and angiogenesis [50]. Lastly, besides soluble factors, growing evidence advances the concept that stem cells can modulate nervous system action as well as the dysregulation of inflammatory responses and immune self-tolerance has to be considered a key element in the autoreactive immune response in MS. To this end, circulating stem/progenitor cells capable of homing in on neovascularization sites [51], and regulatory T-cells (Treg) have emerged as crucial players in the pathogenic scenario of autoimmune inflammation with a role in their modulation by pharmacological and rehabilitation therapy.

### Aims

The primary objective of the study is the verification of the starting hypothesis that RAGT could have greater benefit, compared with conventional therapy alone, in gait speed improvement as assessed by the Timed 25-Foot Walk Test (T25FW).

Secondarily, the study aims to determine whether fatigue, QoL, balance and mobility are improved by RAGT. Finally, the study aims to collect information on whether RAGT or the active control group (CT) influence markers of plasticity, including clinical and circulating biomarkers, and if these modifications are correlated with clinical outcome. The ultimate goal is to draw tailored rehabilitation strategies capable of bypassing the person-specific treatment response in MS patients.

## Methods

### Study design and setting

This study is a parallel-assignment, single-blinded, randomized controlled trial with the assessor blinded to the group allocation of participants (Fig. 1). Participants meeting the inclusion criteria and who provide written informed consent will be randomly assigned to one of the two treatments: the RAGT or the CT group. This study was approved by the Ethics Committee of Ferrara province with approval number 101-2012. This protocol is reported following the Standard Protocol Items: Recommendations for Interventional Trials (SPIRIT) guidelines [52]. A populated SPIRIT Checklist is available as additional file (Additional file 1). Subjects will be recruited using several methods, including the identification of MS patients who are referred to the Rehabilitation Clinics of the Operative Unit of Physical and Rehabilitation Medicine of Ferrara University Hospital and from the Centro Malattie Rare e Neuroimmunitarie, IRCCS Neuroscienze Bellaria, Bologna. All the interventions scheduled, as well as the outcome measure assessment, will be performed at the Operative Unit of Physical and Rehabilitation Medicine of Ferrara University Hospital.

**Fig. 1 Fig1:**
[figure not shown]
Design of the RAGTIME Study. *EDSS* expanded disability status scale, *RAGT* robot-assisted gait training

### Selection criteria and recruitment of participants

Patients affected by primary and secondary progressive MS [53] will be invited to participate if they meet the following inclusion criteria:Men and women, aged 18 to 65 yearsSevere gait impairments, defined by an EDSS score [54] ranging from 6 to 7Ability to perform the T25FWLack of MS worsening in the 3 months just before the intervention periodCognitive functioning to give informed consent identified by a Mini Mental Status Examination (MMSE) score ≥24/30 [55]

Exclusion criteria include:Neurological conditions in addition to MS that may affect motor function and other medical conditions likely to interfere with the ability to complete the study protocol safely, independently from the group assignmentConsiderable muscle spasticity, defined by a Modified Ashworth Scale (MAS) [56] score >3 or contractures that may limit range of motion or function of hip, knee or ankle flexors/extensorsRelapsing of MS-related conditions or changes in drug therapy (both disease-modifying or symptomatic therapies) or any other confounding factor during the studyRehabilitation treatments or botulinum toxin injections during the 3 months preceding the start of the study

During the first meeting with potential participants the physician will ask them if they are interested in taking part in the study; if they are, the physician will address them to a specific screening visit to verify compliance with the inclusion criteria. If compliance is satisfactory, the study physician responsible for inclusion will deliver the letter explaining the study, as well the Consent Form, to the potential participant, and will encourage them to ask any question. After at least 3 days, the patients will be contacted by phone and asked about their decision; in case of voluntary participation, patients will be given an appointment where they will consign the informed consent and where a physiotherapist will perform the baseline outcome measures; if the patients have not yet decided, they will be given adequate time to consider their participation; whereas if the subjects decline participation, they will be thanked for their consideration. According to the Consolidate Standards of Reporting Trials (CONSORT) guidelines [57], the total number of screened subjects who are ineligible (and the reasons for their ineligibility), or who are not willing to participate in the study, will be tracked. To optimize recruitment, all members of the rehabilitation unit of the hospital, including physicians, physiotherapists and nurses, will be contacted weekly by the research coordinator to identify possible participants. Moreover, the research coordinator will participate in the rehabilitation team meetings to check the availability of potentially eligible patients. Information on the study procedures will also be given to the MS support groups.

### Randomization and blinding

After the collection of the informed consent and of the baseline data, the physician responsible for the enrollment will create the allocation sequence, on a personal password-protected computer. The password to log into the allocation list will be given only to the research coordinator, to the physician who created it, and to the administrator responsible of randomization. Then patients will be randomized to one of the two groups by the external administrator not involved in the trial to prevent selection bias through a computerized randomization stratification approach. Participants will be stratified by their degree of impairment (EDSS score) to obtain a balance between groups regarding the baseline physical capacity. The randomization scheme (1:1 ratio) will be set up in permuted blocks of 4 to ensure a similar number of participants between groups. Finally, the subjects will be assigned to one of the two treatment groups: RAGT (experimental group) or CT (active control group). The participants cannot be blinded to the two interventions as the two training protocols were detailed in the informative form for the patients given during the screening visit. Once randomized, patients cannot change the treatment assigned for any reason (e.g., participant request), but in case any medical conditions derived from that specific treatment develop, the training will be immediately suspended. Outcome measure assessors who have to remain blind to group allocation will not have access to the randomization list. Unblinding will not be permissible for these researchers. All outcome data will be recorded on two different electronic spreadsheets by two blinded researchers involved in the trial, and the accuracy of the data will be checked by the research coordinator for all the outcome measures. The privacy of the participants and their personal medical records will be guaranteed by treating the data according to the Italian Law n. 196/2003, to the “Safe Harbor Act” (2000/520/CE) and to the “European Union Data Protection Directive (95/46/EC 24 October 1995).”

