### Outcome assessment and data collection

Outcome measurements will be evaluated at the Operative Unit of Physical and Rehabilitation Medicine of Ferrara University Hospital by the same blinded assessors at the four time points (Fig. 1): (a) baseline (prior to the first intervention session, T0), (b) intermediate (after six training sessions, T1), (c) end of treatment (after the completion of 12 sessions, T2) and (d) follow-up (after 3 months from the end of training program, T3). Before the last outcome assessment, a blinded physiotherapist will contact each participant to remind them to attend the measurements sessions. A summary of the measures to be collected is reported in Table 1. A physician member of the research team involved in the subject enrollment will administer the MMSE and all the other clinical measures (EDSS, MAS) to determine eligibility for each patient. Moreover, the person responsible for the participant selection will record the general demographic information (age, gender), comorbidities and medical history.

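### The enrolling physician writes the allocation list and, like the research coordinator who helps find candidates, can open it, so allocation concealment is not protected

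*Protocol article*

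**What the plan says.** All of the following is in the protocol article.

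- **Who makes the list** (Randomization and blinding): "the physician responsible for the enrollment will create the allocation sequence, on a personal password-protected computer". The sentence places this step "After the collection of the informed consent and of the baseline data".
- **Who can open it** (same section): the password "will be given only to the research coordinator, to the physician who created it, and to the administrator responsible of randomization".
- **The stated safeguard** (same section): "patients will be randomized to one of the two groups by the external administrator not involved in the trial to prevent selection bias".
- **The scheme** (same section): 1:1, stratified by EDSS; it "will be set up in permuted blocks of 4".
- **What the holders do in recruitment** (Selection criteria and recruitment of participants): the study physician in charge of inclusion hands over the study information and the consent form and takes questions. The research coordinator contacts unit staff every week, and attends team meetings, to find possible participants.
- **Who scores the stratification factor** (Outcome assessment and data collection): a research-team physician involved in enrolment administers the EDSS and the other eligibility measures.
- **Status** (Trial status): the trial is recruiting.

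**The concern.** Randomisation prevents selection bias only if those who decide whether and when a patient enters cannot foresee that patient's arm. Here a person in charge of enrolment authors the list and keeps the key, and a second key holder helps find candidates. With sight of the next assignment, someone could bring a candidate forward, delay one, or weigh a borderline eligibility judgement differently. Some exclusion criteria call for judgement, for example whether another medical condition is likely to interfere with safe completion.

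The comparability of the two arms on the primary outcome, gait speed by T25FW, is at stake. The primary analysis is a repeated-measures analysis of variance with treatment and time as its factors (Statistical analyses). Covariance adjustment follows only if a baseline outcome differs between groups (Additional statistical analysis), and it can reach only what was measured.

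**Working it through.** The plan gives no figure to reproduce on this point. The check is a tracing of roles, with one supporting calculation.

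**1. Roles side by side**

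| Role | Part in recruitment | Can open the list |
|---|---|---|
| Physician responsible for enrolment | Enrols patients; writes the list | Yes |
| Research coordinator | Seeks candidates weekly and at team meetings | Yes |
| External administrator | None; makes the assignments | Yes |
| Outcome assessors | None stated beyond the assessments | No |

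Two of the three holders have a part in recruitment.

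**2. Does the timing close the gap?** The sequence is said to be created after consent and baseline data. There are two readings.

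- One list, created once the first patient has given consent and baseline data. This shields at most that patient. A stratified list in blocks of 4 runs ahead, so later assignments can be seen before those patients are screened.
- A new sequence for each patient. Blocks of 4 could not then operate, and the enrolling physician would still be the one producing the assignment.

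Neither reading conceals the allocation from the enrolling physician.

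**3. How much does the list reveal?**

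- *With the list:* the next assignment is known, 100%.
- *Without the list, but knowing past assignments in the stratum:* a 1:1 block of 4 has 6 equally likely orders.
  - Certain assignments: in 2 of the 6 orders the last two places are forced, and in the other 4 only the last place is. This gives (2/6 × 2 + 4/6 × 1)/4 = 1.333/4 = 1/3. It also requires knowing the block size.
  - Best guess (always name the arm that is behind): expected correct guesses per block = 2 + (16/6 − 1)/2 = 2.833, and 2.833/4 = 17/24 = 70.8%.
- *Simple randomisation:* 50%.

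These figures assume complete blocks.

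**4. Would varying the block size solve it?** The same formula gives 1.5 expected correct guesses for a block of 2, and 3 + (64/20 − 1)/2 = 4.1 for a block of 6. With blocks of 2, 4 and 6 equally likely, accuracy is (1.5 + 2.833 + 4.1)/12 = 8.433/12 = 70.3%, against 70.8% for fixed blocks of 4. Varying sizes makes fewer assignments certain but hardly changes the best guess, and does nothing against a person who can read the list. Custody of the list is what matters.

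**The case against.** The strongest reply is that the plan does have safeguards. Assignment is made by someone outside the trial, after consent and baseline. Ineligible patients are tracked with reasons, no patient may change arm after randomisation, and analysis is by intention to treat. Assessors cannot see the list. All of this is true, but none of it stops a list holder from seeing an assignment before the patient is enrolled. The timing rule does mean that late release of each assignment is largely in the plan already; what is missing is sole custody of the list.

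A reader might infer more than the article supports, and the reply is right on these points:

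- *That concealment was breached.* The article gives access; it does not show that anyone used it.
- *That the coordinator enrols patients.* The coordinator looks for candidates. Nothing has the coordinator screen, take consent or score EDSS.
- *That the list's author scores the stratification factor.* The EDSS rater is a physician involved in enrolment. That this is the same physician is plausible but not stated.
- *That no analysis could repair the bias.* Selection on measured factors, such as baseline T25FW or EDSS, can be partly adjusted for with the models in Additional statistical analysis. Selection on unmeasured prognosis would remain.
- *That outcome data are checked unblinded.* The plan says "the accuracy of the data will be checked by the research coordinator for all the outcome measures", and the coordinator could link patients to arms through the list. But two blinded researchers record the data, the primary outcome is timed by photocell as well as by chronometer, and the article does not say that the spreadsheets carry treatment codes. This is a lesser matter of blinded data handling, separate from concealment.

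**Conclusion.** The point holds as a defect of the design as written: upcoming assignments are open to the physician who enrols patients and to the coordinator who helps find them, which defeats the purpose for which the external administrator is named. For a list holder, predictability of the next assignment is 100%, against 50% under simple randomisation.

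The conclusion rests on reading the custody sentences literally and on the list covering more than one patient, which blocking requires. It does not rest on any misuse. No effect on T25FW is estimated, because the article offers no basis for one, and neither the size nor the direction of any bias can be read from it. If custody in practice differs from the text, the text is what needs correcting. The flaw should be corrected before further patients are randomised, since later analysis can only partly make up for it.

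**What to change.** 1. Have the external administrator or the statistical unit generate the sequence and alone hold it.
2. Remove list access for the enrolling physician and the research coordinator.
3. Release each assignment, one patient at a time, only after eligibility, EDSS stratum and baseline T25FW are recorded.
4. As the trial is recruiting, regenerate the unused part of the list under this custody.
5. For patients already randomised, report who had access to the list, and compare baseline characteristics by arm before and after the change. This comparison is descriptive: similar arms would not prove that no selection took place.
6. As a side point, have the coordinator check outcome data without treatment codes.

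Varying the block size is optional and does not replace step 1.

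The cost is a procedural amendment. The external administrator and the statistical unit are already named in the article; that they can take this on without further resources is an assumption. Sample size, visits and the planned analyses do not change.

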### Intervention fidelity and monitoring of adverse events

Before the beginning of the study, treatment physiotherapists will be trained by a member of the research team with a high level of experience in RAGT and CT training of MS patients. Physiotherapists will be provided with 1:1 guidance focused on the treatment’s characteristics and peculiarities, and their ability to complete training sessions will be verified. When the study begins, to each physiotherapist will be given the module to record the specific training administered to each participant. During the whole duration of the study, the members of the research team and research coordinator will randomly visit training sessions, to ensure that the scheduled intervention is being performed accurately and with high adherence to the protocol proposed. Any adverse unpredictable event will be recorded in the registry of each patient and the electronic database of the study, and managed according to the policies of the hospital, with referral for appropriate medical follow-up.

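### A published, fixed block size of 4 within EDSS strata lets anyone who knows a stratum's allocation history name about a third of assignments; varying, undisclosed sizes are a cheap second step after list access is closed

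*Protocol article*

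**What the plan says.** Under Randomization and blinding, the protocol article stratifies by EDSS score and then fixes the scheme: "The randomization scheme (1:1 ratio) will be set up in permuted blocks of 4 to ensure a similar number of participants between groups". It mentions no second block size, no random variation and no withholding of the size. The same section has the enrolling physician create the sequence. It gives the list password to that physician, the research coordinator and the randomization administrator. An external administrator then allocates patients, with the declared aim of avoiding selection bias.

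Four other statements bear on whether past allocations can be learned:

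- Treatment is open: "The participants cannot be blinded to the two interventions as the two training protocols were detailed in the informative form".
- Everything happens in one place (Study design and setting): "All the interventions scheduled, as well as the outcome measure assessment, will be performed at the Operative Unit of Physical and Rehabilitation Medicine of Ferrara".
- The coordinator looks for candidates (Selection criteria and recruitment of participants): "the research coordinator will participate in the rehabilitation team meetings to check the availability of potentially eligible patients". The unit's physicians, physiotherapists and nurses are also asked weekly for candidates.
- Training is observed (Intervention fidelity and monitoring of adverse events): "the members of the research team and research coordinator will randomly visit training sessions".

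A physician involved in enrolment rates the EDSS (Outcome assessment and data collection), and eligibility limits it to 6 to 7. Trial status is given as recruiting.

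**The concern.** In a 1:1 block of known size 4, each arm has two places. Once one arm's places are used, the rest of the block is determined. Someone who knows the block size, the patient's stratum and the stratum's past assignments can work this out by counting, without seeing the list.

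The article discloses the size. The stratum is known to the physician who rates the EDSS, and there can be few strata on a 6 to 7 range. The third ingredient, the allocation history, is plausible because robot training and corridor walking look different, take place in one unit, and are seen by people who also look for candidates.

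If the next arm can be foreseen, the choice of whom to approach and when to book the consent and baseline visit can be steered, even unintentionally. Steering on motivation or expected response would bias the T25FW comparison. The planned repeated-measures ANOVA (treatment, time) would not remove it. The ANCOVA that is planned if baseline outcome levels differ would not remove it either.

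**Working it through.** The article gives no predictability figure, so there is none to reproduce.

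**Inputs from the article.** Block size 4, ratio 1:1, EDSS strata (number not stated, so 1 to 3 assumed), 98 patients with 49 per arm.

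**Certainty with a fixed block of 4.** There are 6 equally likely sequences with two patients per arm. An assignment is certain when one arm's two places are already used.

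- Positions 1 and 2: probability 0.
- Position 3: certain only if the first two went to the same arm, 2/6 = 1/3.
- Position 4: always certain.
- Share certain: (0 + 0 + 1/3 + 1)/4 = 1/3.

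With 98 patients and incomplete last blocks, simulation gives 32.7%, 32.5% and 32.1% for 1, 2 and 3 strata. That is 32.0, 31.8 and 31.4 patients, so the unknown number of strata hardly matters.

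**Best guess with a fixed block of 4.** Guessing the arm that is behind is right with probability 1/2, 2/3, 2/3 and 1 at the four positions. The mean is 17/24 = 70.8%, against 50% with no information.

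**Varying sizes.** The simulated observer knows the set of sizes and all past assignments in the stratum, but not where blocks begin or end. This is pessimistic for the remedy, because the sizes would not be disclosed. The ranges cover 33 to 98 patients per stratum.

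| Block sizes | Certain | Best guess right |
|---|---|---|
| 4, fixed | 32.4–32.7% | 70.2–70.6% |
| 4/6 | 5.6% | 68.6–69.2% |
| 4/6/8 | 2.3–2.4% | 67.3–67.9% |

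**What this could do to the test.** Assume recruiters shift the prognosis of the next patient by v SD toward the arm they expect, at every guess. With best-guess rate p, the expected spurious arm difference is 2v(2p − 1) SD.

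- Fixed 4: 2v(2 × 0.708 − 1) = 0.83v.
- 4/6: 2v(2 × 0.686 − 1) = 0.74v.
- 4/6/8: 2v(2 × 0.672 − 1) = 0.69v.

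With 49 per arm, the noncentrality is this difference times √(49/2) = 4.95. For fixed blocks of 4 it is 0.41, 0.83 and 1.24 at v = 0.1, 0.2 and 0.3. A two-sided 5% t test on 96 degrees of freedom then gives these false-positive rates:

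| v (assumed) | Fixed 4 | 4/6 | 4/6/8 |
|---|---|---|---|
| 0.1 | 6.9% | 6.5% | 6.3% |
| 0.2 | 12.9% | 11.3% | 10.4% |
| 0.3 | 23.2% | 19.4% | 17.3% |

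In this model 4/6/8 removes about one sixth of the bias: (0.83 − 0.69)/0.83 = 17%.

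**A recruiter who acts only when certain.** The bias is 2v times the certain share: 2v × 1/3 = 0.67v for fixed 4, and 2v × 0.023 ≈ 0.05v for 4/6/8. Against simple counting, the remedy removes nearly all of it.

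**The case against.** The strongest objection is factual. A reader might infer that recruiters see all prior allocations, and hence that a third of assignments are in fact known in advance. The article does not say so. Counting needs the complete, ordered history of one stratum, whereas the fidelity visits are random spot checks and nobody is described as keeping a tally. Open treatment in one unit makes such knowledge plausible, not established. This stands, and the one-third figure is therefore conditional.

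Second, as written, the enrolling physician and the coordinator can read every assignment from the list whatever the block size. For them, block size changes nothing until that access is removed. This stands too, and it makes the point secondary. It does not dispose of it, because withdrawing the password would still leave counting possible.

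Third, a reader might attribute the whole rise in false positives under blocks of 4 to the block size. The same model with 4/6/8 still gives about 6%, 10% and 17%, so most of the modelled rise would remain. The steering v has no source in the article. The model also assumes steering at every guess and an unadjusted two-group comparison, whereas the planned analysis includes baseline and so partly handles a shift in baseline level.

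Fourth, the waiting time of at least 3 days before the phone call belongs to the patient and should not be read as a scheduling device for recruiters. Because randomization follows consent and baseline, another patient may enter the stratum in between, so the arm due at invitation need not be the arm due at allocation. This limits steering but does not exclude it, since staff still choose whom to approach and when to book.

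**Conclusion.** The point holds as a secondary weakness of allocation concealment. For anyone who knows the ordered history of an EDSS stratum, the disclosed fixed block of 4 makes about 32–33% of assignments certain (31–32 of 98) and 70.8% guessable. The arithmetic is exact for complete blocks and robust to 1 to 3 strata. That recruiters have this history is an inference from open treatment in one unit whose staff also help recruit.

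The article does not support saying that the fixed block by itself defeats concealment: two thirds of assignments are not certain even to a fully informed observer, and list access is the larger problem. The false-positive rates rest on an assumed v and show only a modest gain from the remedy. The solid gain is the fall in certain assignments from about 32% to about 2% (4/6/8) or about 6% (4/6), and it is realized only if list access is closed as well.

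**What to change.** In Randomization and blinding, replace the fixed block of 4 with permuted blocks of randomly varying size within EDSS stratum. The external administrator should generate and hold the sequence, and the sizes should not be disclosed to anyone who recruits, treats or assesses. In the same amendment, withdraw the enrolling physician's and the coordinator's access to the list, and have the administrator release each assignment singly after consent and baseline data are entered. Neither measure is sufficient alone.

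As the trial is recruiting, this can apply only to blocks not yet opened. The article does not show how many remain, so the benefit at this stage cannot be quantified.

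The cost is a short amendment and regeneration of the unopened part of the list, with no extra patients. The maximum imbalance per stratum rises from 2 to 4 with blocks of up to 8, which has a negligible effect on power at 98 patients.
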